In particular, the first aim will be to assess the short-term and long-term efficacy of tele@cognitive protocol as compared to an unstructured cognitive at-home rehabilitation in the treatment of a cohort of patients with CNDs, monitoring intervention effectiveness by a clinical, functional, neurocognitive, and quality of life assessment applied before treatment (T0), after treatment (5 weeks, T1), and at a 3-month follow up visit (T2). We hypothesize that this digital health at-home intervention would ameliorate cognitive abilities more than unstructured at-home rehabilitation in subjects with SCCs, MCI, and PD. We will also evaluate adherence to the rehabilitation program delivered at-home in the absence of therapist supervision. It is hypothesized that, at an early stage of the disease, cognitive telerehabilitation treatment with innovative digital solutions can bring about positive effects on treatment adherence and difficulties specific to each clinical condition.

The second aim will be to investigate the effects of a cognitive rehabilitative protocol based on a digital health at-home intervention (tele@cognitive) on biomolecular and neurophysiological markers, hypothesizing that people with CNDs enrolled in the tele@cognitive protocol will develop changes in circulating biomarkers and patterns of connectivity. Specifically, at T0 and T1, we will study the effect of tele@cognitive treatment on: i) blood biomarkers reflecting neurodegeneration, amyloid-β, tau and alpha-synuclein pathologies, neuroinflammation, synaptic function, and neuronal communication; ii) neurophysiological responses to TMS over the motor cortex. This approach will give a broad overview of the circuits modulated through telerehabilitation (tele@cognitive treatment), possibly highlighting differential effects between the groups.

Finally, the third aim will be to investigate potential cognitive, neurobiological, and neurophysiological predictors of treatment outcomes in people with CNDs who received innovative technology-enhanced telerehabilitation intervention (tele@cognitive group).

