### 2.2. Randomization and Blinding

The assigned group will be obtained by stratified randomization (1:1 ratio), according to clinical condition, age, and his/her performance in the Montreal Cognitive Assessment (MoCA) test [94,95,96]. Stratified randomization will be achieved by generating a separate block for each combination of covariates, and participants will be assigned to the appropriate block of covariates by a researcher blinded to the study’s aims. Details of the allocated group will be given on cards contained in sequentially numbered, opaque, and sealed envelopes. A blinded researcher will conduct the evaluations.

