### 2.3. Sample Size

In the RCT, patients will be assigned to either receive tele@cognitive protocol or a home-based unstructured cognitive stimulation (ACG). The sample size of the present study was estimated on the basis of a previous work on people within the Alzheimer’s Disease continuum [3] and it was computed on a primary outcome variable (an increase in MoCA score). Applying a two-tailed independent samples *t*-test (alpha = 0.05, beta = 0.80) and considering the effect size (d = 0.784) between two types of intervention (tele@cognitive vs. ACG), we obtained a minimum sample size of 60 subjects (30 per group), taking into account the drop-out rate.

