### 2.8. Statistical Analysis

A repeated-measures analysis will be used to compare pre-treatment (T0) versus post-treatment (T1) and follow-up (T2) clinical, functional, neurocognitive, and quality of life variables for the two groups. Neurophysiological and biochemical data will be analyzed using repeated-measures ANOVAs by comparing the data recorded at T0 and T1. Statistical tests suitable for the data type will be employed to assess the differences between the groups. For continuous variables, independent *t*-tests will be utilized, while chi-square tests will be applied for categorical variables [117,118]. This analysis will verify the effectiveness of the randomization procedure, ensuring that any subsequent comparisons or evaluations between the groups are reliable and valid.

Within-group analyses will be conducted for the tele@cognitive and ACG groups to examine changes from T0 to T1 and T2. Paired *t*-tests or Wilcoxon signed-rank tests, depending on data distribution, will be employed to assess the effectiveness of the intervention over time by analyzing the variations in the collected multimodal parameters [118,119]. Furthermore, a between-group analysis will be conducted to quantitatively compare the outcomes of the two groups. Statistical tests such as independent *t*-tests, analysis of covariance (ANCOVA), or non-parametric tests will be employed, depending on the distributional assumptions and nature of the outcome variables [118,120].

In addition to these statistical analysis, predictive modeling will be implemented to identify key factors associated with treatment outcomes by integrating multimodal data from cognitive assessment, neurophysiological evaluations, biomolecular patterns, and user interaction data within a sophisticated AI framework. Given the heterogeneous nature of the data collected from multiple sources, feature selection is essential to identify the most informative features and reduce dimensionality. This step is critical to eliminate redundant or irrelevant variables and improve model performance [121]. Statistical methods such as chi-square tests and mutual information will be employed to identify significant predictors associated with positive treatment outcomes [122]. Specifically, the dataset will include baseline clinical, functional, neurocognitive, and quality of life measures, biomolecular markers, and neurophysiological parameters.

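### Aim 3 calls the output of a feature screen significant predictors (about 55 baseline measures, at most 30 treated patients), but nothing in the described analysis gives that list an error rate

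*Protocol article*

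**What the plan says.** The third aim, in the Introduction of the protocol article, is to look for potential "predictors of treatment outcomes in people with CNDs who received innovative technology-enhanced telerehabilitation intervention (tele@cognitive group)". It therefore concerns one arm. Section 2.5 plans 30 patients for that arm, half of the 60 under "stratified randomization (1:1 ratio)".

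Section 2.8 presents feature selection as a way to cut dimensionality and drop redundant variables before modelling. It then says what the screen will deliver: "Statistical methods such as chi-square tests and mutual information will be employed to identify significant predictors associated with positive treatment outcomes". On the input it says that "the dataset will include baseline clinical, functional, neurocognitive, and quality of life measures, biomolecular markers, and neurophysiological parameters".

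The rest of 2.8 covers the machine-learning models, cross-validation (leave-one-out or K-fold), accuracy and AUC, and SHAP values to show each feature's contribution to the prediction. The Abstract, Introduction, Discussion and Conclusions all speak of potential predictors, and the trial is called a pilot.

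**The concern.** A filter that feeds a model needs no significance claim. Section 2.8 makes one: features that pass a feature-by-feature association screen are to be identified as significant predictors. With many features and few patients, some will pass by chance.

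The safeguards named in 2.8 address other questions. Cross-validation says how well a model predicts. SHAP says which inputs the fitted model relied on. Neither gives the chance that a feature on the list is unrelated to outcome. Moving the selection inside the cross-validation folds would make the AUC honest, but would still leave the list without an error rate.

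Identifying predictors is the whole of Aim 3, and the Discussion expects them to help shape treatment pathways. A reader who meets the word *significant* in the results will assume an error control that the described procedure does not supply.

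**Working it through.** **1. The plan's own figure.** Section 2.3 gives "alpha = 0.05, beta = 0.80" (0.80 read as power), a "two-tailed independent samples" t-test, and "considering the effect size (d = 0.784").
- Normal approximation: n per arm = 2(1.960 + 0.842)² / 0.784² = 15.70 / 0.6147 = 25.5, so 26. The exact t-test needs 26.5, so 27.
- With 10% drop-out (assumed; no rate is given), 27 / 0.90 = 30 per arm. This agrees with the "minimum sample size of 60 subjects (30 per group), taking into account the drop-out rate".
- The arm size is thus reproduced, and Aim 3 has at most 30 patients. The 0.05 in 2.3 belongs to the MoCA comparison. No level is stated for the Aim 3 screen.

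**2. Number of candidate features**, counted from sections 2.6 and 2.7:
- Primary scores: MoCA 1 + FCSRT 5 = 6.
- Secondary scores: EQ-5D-3L 5 dimensions + visual analog scale 1, MDS-UPDRS parts I and III 2, HDRS 1, STAI-Y 2, NPI 1, EMQ 1, CPM 1, TMT 2, Stroop 2, ROCF copy 1 and recall 1, fluency 2 = 22.
- Blood markers 13; extracellular-vesicle measures 3.
- TMS: rMT 1, MEP amplitude and latency 2, SICI at 4 intervals, SAI at 4 intervals = 11.
- Total 6 + 22 + 13 + 3 + 11 = 55. Without the two MDS-UPDRS parts, which apply to PD only, it is 53. Demographics, cognitive reserve and user-interaction data would add more.

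**3. Independent features, each at exactly 0.05 (assumed level).**
- P(at least one false) = 1 − 0.95^55 = 94.0%; expected false predictors 55 × 0.05 = 2.75.
- A true per-test size of 1 − 0.5^(1/55) = 0.0125 puts the probability at 50%.
- Bonferroni control at 5% would need 0.05 / 55 = 0.00091 per feature.

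**4. Discreteness of chi-square at n = 30.** For a median-split feature against responder status, the exact hypergeometric size s gives 1 − (1 − s)^55 for independent features:

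| Responders of 30 | Uncorrected: s | P(at least one) | Continuity-corrected: s | P(at least one) |
|---|---|---|---|---|
| 8 | 0.0352 | 86% | 0.0352 | 86% |
| 10 | 0.0502 | 94% | 0.0052 | 25% |
| 12 | 0.0604 | 97% | 0.0078 | 35% |
| 15 | 0.0268 | 78% | 0.0268 | 78% |

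**5. Correlated features.** Null simulation with n = 30, normal features in three blocks (28 clinical and cognitive, 16 blood and vesicle, 11 TMS), equal correlation within a block, nominal 0.05 per feature, 20,000 runs. P(at least one false predictor) at within-block correlation 0 / 0.3 / 0.5 / 0.7:

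| Test | 10 responders | 12 responders | 15 responders |
|---|---|---|---|
| Uncorrected chi-square, median split | 94 / 92 / 86 / 77% | 97 / 95 / 91 / 83% | 78 / 74 / 67 / 56% |
| t-test on the numeric scale | 94 / 89 / 78 / 63% | 94 / 88 / 79 / 63% | 94 / 88 / 79 / 63% |
| Continuity-corrected chi-square | 25 / 23 / 21 / 17% | 35 / 33 / 29 / 24% | 78 / 74 / 67 / 56% |

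Correlation leaves the expected number of false predictors almost unchanged: about 2.8, 3.3 and 1.5 for uncorrected chi-square with 10, 12 and 15 responders, and about 2.75 for the t-test. At correlation 0.8, uncorrected chi-square gives about 70% with 10 responders and 49% with 15.

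**The case against.** The strongest reply is that the sentence must be read with those around it. They describe a pre-model filter, and interpretation of individual features is left to SHAP after training. On that reading *significant* is a loose adjective. The aim is worded throughout as potential predictors, in a pilot whose Discussion lists sample size as a limitation. Thresholds and multiplicity rules for a third aim may sit in a full protocol or analysis plan that is not shown.

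Much of this stands, and it rules out stronger readings that a reader might infer:
- **That a false predictor is more likely than not in every case.** The article fixes no level, does not define a positive outcome, and offers chi-square and mutual information only as examples; mutual information has no built-in significance level. A continuity-corrected test with 10 to 12 responders of 30 falls well below one half, and very high correlation brings even the uncorrected test to about one half.
- **That every feature will be cut at its median and tested by chi-square.** The article does not say so. For the between-group checks in the same section it gives chi-square to categorical variables and t-tests to continuous ones. The median split above only serves to size the problem.
- **That the plan has no ranking of features.** SHAP provides one, though without an error rate.
- **That the missing multiplicity rule is itself the error.** In a condensed article it is not.

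What the reply does not remove is the sentence itself. It attaches a significance claim to the output of the screen and goes further than the aim it serves.

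**Conclusion.** The point holds in a limited form. Section 2.8 promises significant predictors from a screen of about 55 features in at most 30 patients, and nothing else described there supports that word.

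If features were retained at 0.05 each, the chance of at least one false name in a null dataset is roughly 56 to 97% for uncorrected chi-square or numeric-scale tests, and about 17 to 35% for a continuity-corrected test with 10 to 12 responders. Even the lowest of these is more than three times 5%. The figures rest on the assumed 0.05 level, 30 analysed patients, 10 to 15 responders, and equal within-block correlation of 0 to 0.7. The size of the problem therefore depends on choices the article leaves open, but the mismatch between the label and the procedure does not.

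This affects what Aim 3 may conclude. It does not touch the randomised comparison. It should be changed, and the change is cheap.

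**What to change.** In section 2.8:
1. Replace *significant predictors* with *candidate features*, and state that the screen is an exploratory filter ahead of the models. This brings 2.8 into line with the potential predictors of the aims.
2. Report how often each feature is selected across resamples.
3. If significance is to be claimed for any feature, base it on permuting the outcome and repeating the whole screen each time (max-statistic p-value), or on a stated false discovery rate over all screened features.

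Testing numeric features on their own scale is sensible, but it does not replace step 3: without error control it still gives 63 to 94% in the working above.

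The cost is a few lines of text and some computing time, with no new data. The downside is a shorter list of claimed predictors, possibly none.

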### 2.4. Participants

According to the sample size calculation, the EARLY-COGN^3 trial has a target enrollment of 60 subjects with CNDs (MCI, SCCs, and PD).

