### 2.5. Intervention Procedures

The cognitive rehabilitation protocol (5 weeks, 3 sessions/week, 45 min/session) will be delivered to all participants according to the corresponding experimental group:-30 CNDs patients will receive home-based cognitive rehabilitation activities with an innovative digital solution for remote rehabilitation of cognitive difficulties (tele@cognitive group);-30 CNDs patients will receive home-based unstructured cognitive rehabilitation treatment (Active Control Group—ACG).

The technological solution that will be applied in the tele@cognitive group consists of: (a) a telemedicine platform (RICORDO platform), which allows prescription and planning of digital content for cognitive rehabilitation and monitoring of the rehabilitation cycle and (b) RICORDO application [http://www.ricordo-dtx.com/ (accessed on 10 January 2025)] that will be downloaded on tablets provided to patients by the recruiting units, which will allow the patient to benefit from personalized rehabilitation treatment remotely and in asynchronous mode. In detail, through RICORDO platform, the clinician will have the possibility of prescribing, within the patient’s Individual Rehabilitation Plan (PRI), a personalized intervention that will involve the use of libraries of digital rehabilitation content that maps all the neurocognitive domains provided for in the most recent version of the Diagnostic and Statistical Manual of Mental Disorders (DSM-5) [102]. In particular, the rehabilitation program will include cognitive activities focused on cognitive domains, such as executive functions, memory (long-term memory of both verbal and visuospatial type, autobiographical memory, and semantic memory), attention (selective attention and divided attention), and spatial–temporal orientation and language. Each cognitive exercise will be structured into five levels of difficulty that adaptively increase (algorithms on both subject’s performance and perceived difficulty). All data on patient progress and adherence will be collected and will be available to evaluate and monitor the results of rehabilitation.

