### 2.7. Data Collection

Demographic characteristics and cognitive reserve, evaluated with the Cognitive Reserve Index—questionnaire (CRI-q [116]), will be collected at the baseline evaluation (T0). The same trained neuropsychologist (blinded to patient treatment allocations) will assess primary and secondary outcome measures for a single patient in all visits (T0, T1, and T2). Neurophysiological and biomolecular data will be collected only at the baseline (T0) and at post-treatment (at 5 weeks, T1). A subjective assessment of the digital system’s usability will be performed at T1 using the System Usability Scale (SUS) [117], a 10-item attitude Likert scale. Best practices and standards will be adopted for the collection, storage, and treatment of the data. Clinical, functional, neurocognitive, and quality of life assessment data will be collected by clinicians and stored in a specific dataset. Data will be pseudo-anonymized so that they will not be linkable to the identities of the subjects. Neurophysiological data will be organized according to Brain Imaging Data Structure (BIDS) for non-invasive brain stimulation studies and safely stored in a dataset. Biological samples collected at T0 and T1 will be stored at −80 °C until the analyses. Biomolecular data will be safely stored in a dataset. Informed consent will be obtained from patients for the storage of all data. In more detail, the data collection in terms of data collected and tools will include:

[AIM1] Clinical, functional, neurocognitive, and quality of life data recorded at T0 (baseline), T1 (post-treatment, at 5 weeks), and T2 (3-month follow-up visit).

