Data will be preprocessed to clean and normalize them appropriately. These will include handling missing values (e.g., using imputation for continuous variables and mode replacement for categorical variables), standardizing features to a common scale, and encoding categorical variables as needed. Machine learning algorithms, such as random forests, support vector machines, naive bayes classifiers, and ensemble techniques, will be applied to develop predictive models for treatment outcomes using the collected information [123]. Model performance will be assessed using cross-validation techniques like leave-one-out or Kfold, and parameters will be fine-tuned using grid search techniques to optimize model performance [124]. To ensure generalizability, performance will also be evaluated using metrics such as accuracy, precision, recall, and area under the ROC curve (AUC-ROC), depending on the nature of the prediction task.

For tasks involving high-dimensional or complex data, such as neurophysiological signals or time-series patterns, deep learning architectures (e.g., convolutional neural networks for spatial data, recurrent neural networks for temporal data) will be employed. These models will be customized and optimized using grid search to ensure they are well-suited to the specific characteristics of the data.

After model training, explainable AI (XAI) techniques, such as SHAP (Shapley Additive exPlanations) values will be employed to interpret the model’s predictions and quantify the contribution of each feature to the outcome [125]. SHAP values provide a unified measure of feature importance by assessing the impact of individual features on the model’s output, not only enhancing the clinical interpretability and transparency of the predictive models but also providing insights into which factors are most influential in driving treatment outcomes.

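### Aim 3 pools three diseases and states no step that separates a marker's link with response from diagnosis, so a marker that only labels the disease can be named a predictor

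*Protocol article*

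**What the plan says.** The Introduction restricts the third aim to one arm and takes the diagnoses together: it concerns "predictors of treatment outcomes in people with CNDs who received innovative technology-enhanced telerehabilitation intervention (tele@cognitive group"). Section 2.5 puts that arm at 30: "30 CNDs patients will receive home-based cognitive rehabilitation activities with an innovative digital solution".

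Section 2.8 describes the candidate features: "the dataset will include baseline clinical, functional, neurocognitive, and quality of life measures, biomolecular markers, and neurophysiological parameters". It then sets the selection step: "Statistical methods such as chi-square tests and mutual information will be employed to identify significant predictors associated with positive treatment outcomes". Random forests, support vector machines, naive Bayes and ensemble methods follow, with cross-validation. SHAP values are then read as "providing insights into which factors are most influential in driving treatment outcomes".

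The Introduction (second aim) describes the blood markers as "blood biomarkers reflecting neurodegeneration, amyloid-β, tau and alpha-synuclein pathologies, neuroinflammation, synaptic function, and neuronal communication".

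Section 2.2 makes clinical condition a stratification factor for allocation. Section 2.8 gives it no role in Aim 3: there is no adjustment for diagnosis, no screening within diagnosis and no comparison with a model that holds diagnosis alone.

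**The concern.** Two features of the protocol make diagnosis a likely confounder of any marker-response association.

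- **Markers.** Several candidates are presented as indicators of particular pathologies, so their levels may differ between SCCs, MCI and PD.
- **Response.** The Introduction notes that people with SCCs can perform normally on objective tests, and section 2.6.1 caps the MoCA at 30. Room to gain may therefore differ by diagnosis.

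When both differ, a marker that has nothing to do with response inside any disease is still associated with response in the pooled arm. Three safeguards in the plan do not remove this:

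- Cross-validation does not, because such a marker really does predict in held-out patients, by way of diagnosis.
- Stratified allocation balances the two arms. It does not separate marker from diagnosis within one arm.
- SHAP credits whatever feature the model uses, including one that stands in for diagnosis.

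At stake is how Aim 3 is interpreted. A blood or TMS measure could be reported as a neurobiological predictor when the finding is only that the diseases respond differently, which needs no blood draw or TMS. The Discussion and Conclusions intend these predictors to inform treatment pathways.

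**Working it through.** **The plan's own figure.** The protocol gives no figure for Aim 3, only the total of 60 for the MoCA comparison (section 2.3). With d = 0.784, two-sided alpha 0.05 and the stated beta of 0.80 read as power 0.80, the normal formula gives 2 × (1.960 + 0.842)² / 0.784² = 25.5, so 26 per arm. The t-test gives 26.5, so 27. An assumed 10% dropout gives 27 / 0.9 = 30 per arm, which reproduces 60. Aim 3 therefore has 30 people, or about 27 completers under that dropout.

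**Assumptions.** The protocol fixes no case mix, so 10 per diagnosis is assumed. One diagnosis has its marker mean shifted by a SD and its outcome mean shifted by b SD. Marker and outcome are independent within each diagnosis.

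**Induced pooled correlation.** With one third of patients shifted, the between-diagnosis covariance is (1/3)(2/3)ab = 2ab/9, so

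ρ = (2ab/9) / √[(1 + 2a²/9)(1 + 2b²/9)].

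The chance of p < 0.05 is approximated with z = atanh(ρ) × √27 and compared with simulation (20,000 datasets per setting, n = 30):

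| a, b | ρ | z | approximation | simulated, unadjusted |
|---|---|---|---|---|
| 1, 0.5 | 0.098 | 0.51 | 8.0% | 8.1% |
| 1, 0.8 | 0.150 | 0.79 | 12.4% | 12.6% |
| 1.5, 0.8 | 0.204 | 1.07 | 18.9% | 19.6% |
| 1.5, 1.0 | 0.246 | 1.31 | 25.7% | 26.6% |

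Adjusted for diagnosis, the simulated rate is 5.0 to 5.2%.

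**The named test.** A median-split chi-square at n = 30 flags the same marker in about 3.5 to 11% of datasets. Its null size is about 2.7%, because a 2 × 2 table this small takes few values. At n = 27 it gives 9 to 22% against a null size of 5.8%, and about 2 to 5% with a continuity correction. The absolute rate thus depends heavily on the test and on n, but the rise over the same test's null size is present at n = 30 as well.

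**Binary response, larger contrasts.** Marker means 0, 1 and 2 SD across the three diagnoses, n = 30:

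| Response rates | pooled t-test | pooled chi-square | adjusted for diagnosis |
|---|---|---|---|
| 50/50/50% | 5.0% | 4.2% | 4.8% |
| 40/50/60% | 8.4% | 7.2% | 5.0% |
| 30/50/70% | 20.6% | 15.6% | 5.1% |
| 20/50/80% | 42.5% | 30.6% | 5.1% |

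The first row shows that nothing happens when response does not differ by diagnosis.

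**What diagnosis alone can score.** If responders are 7, 5 and 2 of 10, non-responders are 3, 5 and 8. Concordant pairs are 7 × 13 + 5 × 8 = 131, tied pairs are 21 + 25 + 16 = 62, and all pairs are 14 × 16 = 224. The AUC is (131 + 31) / 224 = 0.72. The same sum gives 0.59 for 6/5/4 and 0.77 for 8/5/2. A marker model could absorb this and be credited with it.

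**The case against.** The strongest reply is that this is detail a condensed article leaves to the analysis plan, and that nothing in the text excludes diagnosis. The filters are introduced by an illustrative phrase, the later models are multivariable, and diagnosis could sit under baseline clinical measures, pass the filter and compete with the markers. That stands in part: the one-at-a-time step is not the whole of Aim 3. But the article itself fixes a pooled population, names marginal filters and states how SHAP will be read. Diagnosis as one feature among many gives no adjusted association and no benchmark for what a marker adds.

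The sizes are assumed, and this also stands. Correlation is not the test named for the screen, and the named chi-square shows a much smaller absolute rate at n = 30.

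It can also be said that a marker predicting through diagnosis is still a predictor, and that the protocol speaks of potential predictors. That is fair for prediction, less so for the causal reading of SHAP.

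A reader might further infer that the predictor set leaves out demographics and cognitive reserve, since the feature list does not name them. The documents do not support this. Section 2.7 collects "Demographic characteristics and cognitive reserve, evaluated with the Cognitive Reserve Index—questionnaire" at baseline, the list in section 2.8 is open (the same paragraph adds user interaction data, which the list lacks), and modelling is to use the information collected. Nor does the text support saying that Aim 3 will give a wrong answer: it can, under conditions the protocol does not quantify.

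**Conclusion.** The point holds in a limited form. As written, the route allows a marker that only distinguishes the diseases to be reported as a predictor of response, and no stated step would reveal it. This requires marker level and response both to differ by diagnosis. The protocol makes that plausible and gives no figures for it. Under moderate assumed shifts and an equal case mix, the rate at n = 30 is 8 to 27% by correlation (null about 5%) and about 3.5 to 11% by median-split chi-square (null about 2.7%), with the correlation back at about 5% after adjustment. With equal response there is no excess. The primary comparison of the arms is not affected.

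**What to change.** In section 2.8, for Aim 3:

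1. Carry diagnosis and baseline score as forced terms.
2. Report each biomolecular or TMS marker's association with response adjusted for diagnosis.
3. Show the cross-validated performance of a small penalised model with diagnosis and baseline score only, beside that of the marker model.
4. Describe a marker as a predictor beyond diagnosis only on that evidence, and label Aim 3 exploratory.

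The cost is wording and one extra model. Diagnosis and the baseline score are already recorded. The statistical price is about three degrees of freedom (two for diagnosis, one for baseline score) in at most 30 people, hence the penalty, and some loss of signal that lies between diseases. Unadjusted results can be shown alongside for that reason. A larger reference model, or a rule that suppresses any marker that does not improve cross-validated performance, would be too heavy and too noisy at this sample size and is not proposed.

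### Section 2.8 does not require outcome-driven feature selection and tuning to be repeated inside the training folds, and offers only a list of metrics as protection for generalizability

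*Protocol article*

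**What the plan says.** The relevant text is in the protocol article, section 2.8 (Statistical Analysis).

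- **Feature selection.** The article treats it as essential and makes it outcome-driven: "Statistical methods such as chi-square tests and mutual information will be employed to identify significant predictors associated with positive treatment outcomes".
- **Preprocessing.** Imputation, scaling and encoding are listed next, without reference to folds.
- **Validation and tuning.** After naming several algorithm families, it says: "Model performance will be assessed using cross-validation techniques like leave-one-out or Kfold, and parameters will be fine-tuned using grid search techniques". This is one layer of cross-validation plus a grid search. No inner and outer loop, hold-out set or external data set is named.
- **Safeguard.** "To ensure generalizability, performance will also be evaluated using metrics such as accuracy, precision, recall, and area under the ROC curve".
- **Further models.** For signal or time-series data, "deep learning architectures (e.g., convolutional neural networks for spatial data, recurrent neural networks for temporal data) will be employed". SHAP values are then used to rank the features.

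The Introduction restricts Aim 3 to patients who received the tele@cognitive treatment, and section 2.5 puts 30 patients in that arm.

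**The concern.** A filter that ranks features by their association with the outcome has already used the outcome of every patient it sees. If it runs once on all patients, each later test fold contains patients who helped choose the features, and cross-validation no longer estimates performance in new patients. Tuning on the same folds that supply the reported figure adds a smaller bias of the same kind.

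The sentence on generalizability does not help. Accuracy, precision, recall and AUC computed on leaked folds all inherit the leak.

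Predictors of response are one of the trial's three aims, and the Conclusions expect them to open the way to better treatment pathways. A leaked model could show a high AUC and a persuasive SHAP ranking for features that carry no signal. The randomised comparison of the two arms is not affected.

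**Working it through.** **1. Patients.** Section 2.3 states: "we obtained a minimum sample size of 60 subjects (30 per group), taking into account the drop-out rate". With two-sided alpha 0.05, power 0.80 and d = 0.784, the normal approximation is

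n per arm = 2(1.960 + 0.842)² / 0.784² = 2 × 7.85 / 0.615 ≈ 25.5, so 26.

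The exact t calculation gives 27 per arm (power 0.807), and 27 / 0.90 = 30. The plan's 30 per arm is reproduced if dropout is 10%. That rate is an assumption, because none is printed. (The printed "alpha = 0.05, beta = 0.80" is read as power; taken literally as a type II error it would need only about 5 per arm.) The Aim 3 model therefore has at most 30 patients before dropout.

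**2. Candidate features.** The article gives no count. From sections 2.6 and 2.7:

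- Clinical and cognitive: MoCA 1, FCSRT 5, EQ-5D-3L 6, MDS-UPDRS parts 2 (PD only), HDRS 1, STAI-Y 2, NPI 1, EMQ 1, CPM 1, TMT 2, Stroop 2, ROCF copy 1, fluency 2, ROCF recall 1, CRI-q 1 = 29
- Blood: 13 analytes + 3 vesicle measures = 16
- TMS: rMT 1, MEP 2, SICI 4, SAI 4 = 11

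Total 29 + 16 + 11 = 56. Demographics bring it close to 60, before any app-usage data.

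**3. Simulation on pure noise.** Assumptions: independent normal features; balanced binary response; a t-statistic filter standing in for chi-square or mutual information; Gaussian naive Bayes; 5-fold cross-validation; an 18-point grid (3, 5 or 10 features × 3 smoothing values × pooled or separate variance). Tuning outside the folds means reporting the best grid value of the metric shown. The true AUC and accuracy are 0.50. There were 300 replicates, 100 for the nested row.

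30 patients, 60 features:

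| Done on the full data | Mean AUC | Accuracy | AUC ≥ 0.70 | AUC ≥ 0.80 |
|---|---|---|---|---|
| Selection, no tuning | 0.83 | 0.76 | 98% | 72% |
| Selection and tuning | 0.88 | 0.83 | 100% | 91% |
| Tuning only | 0.59 | 0.60 | 22% | 6% |
| Imputation and scaling only (10% missing, assumed) | 0.50 | 0.51 | 7% | 1% |
| Nothing (fully nested) | 0.51 | 0.50 | 15% | 3% |

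Share of the excess due to selection: (0.832 − 0.50) / (0.876 − 0.50) = 0.332 / 0.376 ≈ 88%.

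**4. Range over the unknown inputs** (200 replicates each):

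| Patients, features | Selection outside | Selection and tuning outside | Fully nested |
|---|---|---|---|
| 30, 30 | 0.76 | 0.80 | 0.49 |
| 30, 100 | 0.87 | 0.92 | 0.54 |
| 24, 60 | 0.86 | 0.91 | 0.48 |
| 60, 60 (both arms) | 0.75 | 0.79 | 0.50 |

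A different set-up (27 or 30 patients, 60 features, the top 5 or 10 kept, no grid, 400 data sets) gave 0.79 to 0.81 with selection outside the folds and 0.49 to 0.50 with selection inside.

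**5. What nesting leaves.** The mean bias goes, but 15% of nested noise runs still reach 0.70. The Monte Carlo standard error is √(0.15 × 0.85 / 100) ≈ 3.6 points. The nested row averages five fold AUCs while the other rows pool the scores, so its tail percentages are not strictly comparable with theirs.

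**The case against.** The strongest reply is that the article never says these steps run on the full data. It is a condensed account, and fold structure may be set out in a full protocol or analysis plan that is not shown. Sentence order is not execution order: chi-square and mutual-information filters normally need complete, encoded data, yet selection is described before cleaning. **This stands.** A reader might infer that selection and tuning are not nested and that the reported AUC will look good on noise. The documents support neither as a flat statement.

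It also stands that imputation and scaling should not be counted as causes (AUC 0.50 in the check), that no tuning criterion is named, that the article does not say the best of several algorithms will be reported, and that neither the feature count nor the definition of response is fixed. Aim 3 is exploratory, in a pilot, and seeks only potential predictors.

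A reader might further conclude that the deep learning step must be deleted, the model list cut to one or two, or SHAP withheld unless a test is passed. The article confines deep learning to high-dimensional or complex data such as signals and time series, which the simulated table does not represent. These would be preferences, not consequences of this point.

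What the reply does not remove: section 2.8 does describe the workflow in detail (selection tests, algorithms, validation, tuning, metrics, SHAP), and in doing so presents metrics as what secures generalizability. That sentence is wrong whatever another document says.

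**Conclusion.** The point holds in conditional form. Section 2.8 combines outcome-supervised selection, a single described layer of cross-validation and grid search, does not require selection and tuning to be repeated within the training folds, and relies on metrics that cannot do the job claimed for them.

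If selection and tuning use the full data, noise yields an AUC of about 0.8 to 0.9 (0.88 at 30 patients and 60 features; 0.79 to 0.92 over the range tried), against about 0.5 when nested. The size rests on the assumed feature count, balanced response, filter, classifier and grid; the direction held in every setting tried. The plan should be corrected, but the primary randomised comparison does not depend on it.

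**What to change.** Replace the sentence that offers metrics as the safeguard with a statement that performance is estimated by nested cross-validation, preferably repeated and stratified, in which supervised feature selection, grid search and any choice among algorithms are done only within the training folds. Report the outer-fold AUC with a confidence interval and a label-permutation p-value, and describe SHAP rankings as hypothesis-generating. Fitting imputation and scaling within the folds is tidy but is not what removes the bias.

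The cost is wording, a pipeline setting and more compute time; no extra patients or data are needed. Reported performance will probably be less favourable. Nesting removes the mean bias, not the imprecision of 30 patients, which is why the interval and permutation test belong with it.
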